### Criteria for discontinuing or modifying allocated interventions {11b}

The randomised entity in this study is the donor liver. Randomised livers that are not perfused due to unforeseen reasons will not be replaced. It is anticipated that non-perfusion of a randomised liver will be a very uncommon event

### Strategies to improve adherence to interventions {11c}

Perfusions will be carried out by members of the central trial team who have experience in delivering the intervention from preclinical studies. Delegated staff at each recruiting centre have completed training for imputation of trial related data onto the MACRO™ database. These tasks will be performed under the supervision of the PI at each site. In addition, the DeFat study has utilised the NIHR Associate PI scheme with an identified delegate to support adherence to monitoring of outcome measures. Comprehensive details are also provided in the DeFat study manual summarising trial related procedures.

### Relevant concomitant care permitted or prohibited during the trial {11d}

Following randomisation the liver will be allocated to either the standard NMP protocol or the NMP-defatting protocol. Transplantation of the liver will be based on ex-situ function and at the discretion of the implanting surgeon. Recipient management including the implantation procedure, postoperative care, immunosuppression and other medications, and post-transplant monitoring will follow local protocols.

### Provisions for post-trial care {30}

Routine blood samples taken for this study are part of standard clinical care and will be processed in local laboratories for clinical purposes as per normal protocols. For study purposes, the results of these investigations will be documented.

### Outcomes {12}

#### Primary outcome measure

To confirm the safety and assess efficacy of the NMP-defatting protocol in steatotic donor livers intended for transplant.

The primary endpoint is the proportion of livers that achieve all of the following functional criteria at 6 h of perfusion [15, 17], as defined by:Clearance of lactate to a level < 2.5 mmol/LPerfusate pH ≥ 7.20Evidence of glucose metabolism (spontaneous fall in perfusate glucose)Minimum bile pH ≥ 7.5 (if bile produced)Bile glucose concentration ≤3 mmol/L or ≥10 mmol less than perfusate glucoseHepatic arterial flow ≥100 mL/min; portal venous flow ≥ 500 mL/minPerfusate alanine aminotransferase (ALT) < 6000 U/L at 6 h

These objective criteria, reflecting hepatic metabolism and injury, have been derived by a process of consensus amongst current NMP users. These parameters are increasingly recognised as a way to discriminate livers with favourable post-transplant outcomes and will be measured at baseline (pre-NMP) and throughout perfusion (1, 2, 4 and 6 h and end of perfusion) [15, 17]. Lactate measurements will also be taken at baseline (pre-NMP) and 5 min after start of NMP.

These functional criteria are not intended as an instruction to the implanting surgeon, but rather as a consistent endpoint for the trial. The decision as to whether a liver is actually transplanted will remain with the implanting surgeon, who will base this on a number of criteria, including some that are recipient-related rather than donor organ-related (e.g. the urgency with which the patient needs a transplant may determine the decision).

#### Secondary outcome measures

ClinicalProportion of livers transplanted in the two armsLiMAx (maximum liver function capacity) test performed after 1 h of liver stabilisation during NMP, repeated at 5 h and subsequently every 6 h till end of perfusion where feasible. If the decision to transplant has been made by 6 h of NMP, the test will not be repeated. The LiMAx test will allow real-time monitoring of CYP1A2 (prominent in functional livers cells and less prominent in damaged cells) and is based on the metabolism of ^13^C-methacetin. This will enable measurement of liver capacity and functional reserve during perfusion [60].Cell-free DNA (cfDNA) measured at baseline (pre-NMP) and during preservation (1, 2, 4 and 6 h and end of perfusion). Further measurements taken from the recipient peri-operatively (before transplant) and re-perfusion (following liver transplantation). Post-operative samples collected on days 1, 3, 7 and 14 (if the patient is discharged prior to day 14—a sample will be collected on the day of discharge instead). Outpatient sample collection will align with clinic visits on day 30 and months 3 and 6. cfDNA has been correlated with allograft injury, rejection and formation of de novo donor-specific antibodies [61].Biochemical liver function in the first 7 days post-transplant: ALT, GGT, INR, bilirubin and peak serum AST (where AST measurements available) in the first 7 days post-transplant. Peak serum AST is a validated surrogate marker, predictive of PNF as well as graft and patient survival [62]. It is also associated with histological evidence of moderate to severe reperfusion injury [63].Model of Early Allograft Function (MEAF) [64]: a score (between 0 and 10) based on bilirubin, INR and ALT within the first three post-operative days.Primary non-function (PNF): irreversible graft dysfunction requiring emergency liver replacement during the first 10 days after liver transplantation, in the absence of technical or immunological causes.Post-reperfusion syndrome (PRS) [65]: a decrease in mean arterial pressure (MAP) of more than 30% for more than 1 min during the first 5 min after reperfusion [65].Need for renal replacement therapy (haemodialysis, haemofiltration, peritoneal dialysis) during the first 7 days post-operatively.Duration of ITU/HDU and hospital stay.Graft survival (defined as a functioning transplant in the absence of death and re-transplantation) at day 7, day 30, month 3 and month 6.Patient survival at day 7, day 30 and months 3 and month 6. In addition, 12-month clinical outcomes (obtained from NHSBT registry) will also be reported:aGraft and patient survivalbTotal number of days in hospital in the last year (excluding transplant admission)cTotal number of re-admissions for:•Recipient infection•Acute rejection•Chronic rejection•Biliary complications•Vascular complications•Disease recurrence•Other reasonsdTransplant-related renal dysfunctioneBiochemistry (liver and renal function)The following safety information will be recorded:aOrgan discard ratebPerfusate culture. At the end of preservation, a sample will be taken for microbiological culture.cAdverse event rates and severity, graded according to the Clavien–Dindo classification [66] during the first 7 days, day 30, month 3 and month 6:•Recipient infection•Biopsy proven acute rejection•Biliary complications (biliary strictures—anastomotic and non-anastomotic, bile duct leaks)•Vascular complications (bleeding, hepatic artery stenosis, hepatic artery thrombosis, portal vein thrombosis)•Reoperation ratedTechnical complications/device failures

Histological and biochemicalCorrelation of pre-perfusion donor biopsy (histopathologist’s steatosis report) with:aWC, BMI and clinical risk scores such as the fatty liver index (FLI) and hepatic steatosis index (HSI) [67, 68] where relevant data availablebSurgeon’s assessment [57]cNon-invasive pocket-sized micro-spectrometer reading. The device has been developed by SCIO - Consumer Physics (http://www.consumer-physics.com) and is CE marked. It utilises spectroscopy (absorption of near infrared light, 700–1100 nm). The commercially available device is able to quantify composition of foods, estimate body fat levels and identify analgesic agents [69]. Readings will be taken sequentially over perfusion (where feasible): at baseline (pre-NMP) and during preservation (1 and 6 h and end of perfusion) to facilitate correlation with post-perfusion (end-NMP) biopsy in addition to the pre-perfusion biopsy.Histological and biochemical evidence of ischaemia–reperfusion injury (IRI):aHistology (formalin fixed paraffin embedded) [33]:(i)Neutrophil infiltration and leucocytosis determined using haematoxylin and eosin (H&E) stain(ii)Glycogen depletion determined using periodic acid-Schiff (PAS) stain(iii)Lipid peroxidation determined using 4-HNE (4-hydroxynonenal) stain

Biopsy samples collected pre-perfusion, post-perfusion and re-perfusion in the recipient (following liver transplantation).
bCytokine profile  implicated in liver transplantation including [70]: CXCl8/IL-8, IL-10, IL-2, TNF-a, IFN-γ, IL-13, IL-4, IL-1β, IL-17A and IL-6.

Blood samples collected peri-operatively (before transplant) and re-perfusion in the recipient (following liver transplantation).

3.Histological and biochemical evidence of bile duct injury (BDI) and biliary viability [71] such as:aHistology (formalin-fixed paraffin embedded) biopsy samples pre-perfusion, post-perfusion and following re-perfusion in the recipient (following liver transplantation). For example, evidence of stromal necrosis, loss/injury to peribiliary glands and vascular lesions. Bile duct biopsies will only be taken if sufficient length on the bile duct and feasible to do so.bBile composition measurements (if produced and measured at 1, 2, 4 and 6 h and end of perfusion) for example: low pH and bicarbonate with high glucose and lactate dehydrogenase (LDH) as indicators of poor biliary viability.

ImagingBiliary strictures (anastomotic and non-anastomotic) determined by MRI scan at month 6 (±1 month) depending on site capacity using MRCP^+^ (a CE-marked advanced biliary visualisation software by Perspectum Diagnostics) [72].Graft hepatic steatosis determined using multiparametric liver MRI (proton density fat fraction, cT1 and T2* mapping) at 6 (± 1 month) depending on site capacity. MRI proton density fat fraction (MRI-PDFF) has demonstrated high diagnostic accuracy in both the detection and grading of hepatic steatosis with histology as a reference standard [73, 74]. CE-marked software such as Liver*MultiScan*^TM^ developed by Perspectum Diagnostics will aide in the quantification of steatosis.

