**Fig. 4 Fig4:**
[figure not shown]
**A–D** Group 1 NMP alone, Group 2 filter and Group 3 filter plus defatting agents

The combination of lipoprotein apheresis filtration and defatting interventions significantly reduced the amount of fat within the liver by 45% at 48 h. However, the functional improvements were seen much earlier, by 6 h. From this experimental study, we concluded that a combination of lipoprotein apheresis filtration and perfusate modification reduces hepatic steatosis and improves ex-situ liver function.

Overall, the pre-clinical studies of ex-situ defatting in discarded human livers, from both Oxford and Birmingham, have demonstrated a ‘proof of concept’ [27, 33]: if this translates into clinical practice, it will significantly increase the number of safely transplantable organs by increasing utilisation of ‘marginal’ organs. The interventional agents proposed are safe, well-tolerated and available for clinical use (in contrast to previous studies) [22, 27]. We do not anticipate any systemic side effects following transplantation; first, because the doses are much lower than those used in human studies and, second, because these agents will be administered ex-situ to livers that are then thoroughly flushed prior to transplant (as per standard practice following NMP) removing the agents from the liver prior to transplantation.

In our discarded liver study, structural and functional differences were evident after 6 h of perfusion. These were associated with improved perfusion and biochemical metrics that would have rendered these organs transplantable on current functional criteria. This suggests that 6 h of perfusion should be the minimum required prior to considering implantation of the organ into the recipient (with a maximum of 24 h as per OrganOx *metra*^*®*^ instructions for use).

In the proposed trial, we intend to enrol livers that have been retrieved for the purpose of transplantation and that have been identified as high-risk of steatosis. We know that such livers are likely to be discarded after retrieval either because of appearance, histology or unfavourable perfusion metrics on NMP. We will test the targeted defatting protocol described above, using objective measures of function to assess outcomes.

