### Explanation for the choice of comparators {6b}

#### NMP (control group)

All livers included in the study will undergo NMP using the OrganOx *metra*^*®*^, a CE-marked device already in use in liver transplant units in both clinical trials and routine clinical practice (providing special arrangement for consent, governance, audit and research) [14, 59].

Livers will be transported on ice to the transplant centre, and those meeting the inclusion criteria will undergo NMP (minimum 6 h, maximum 24 h), in accordance with the manufacturer’s instructions for use and current local protocols. The procedure for preparing the device for use and placing the organ on the device is described in detail in the instructions for use (IFU) document (L300-0437ReV1.0 RoW Version 25/09/2017). All livers will be perfused with three units of donor-type (or O-negative) red blood cells and will be arranged by the recipient surgical team at the recruiting liver transplant centre.

The procedure for removing the liver from the device is also described in the IFU. Implantation and reperfusion of the liver proceed as per the usual practice of the implanting centre.

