### Intervention description {11a}

#### NMP with defatting interventions (study group)

The study arm of this trial combines the use of a lipoprotein apheresis filter to the normothermic circuit (for a minimum of 6 h and a maximum of 24 h), with targeted pharmacological strategies during ex-situ perfusion. Therefore, in addition to NMP, livers randomised to the study group will undergo the defatting protocol developed in our previous experimental study [33]. All components of this protocol are licensed for clinical use and are described in detail in the background section of this protocol. Briefly, these include:Lipoprotein apheresis filtration: this is licensed for patients with severe hyperlipidaemia refractory to maximal medical therapy [34].L-carnitine: this is licensed for use in primary carnitine deficiency due to inborn errors of metabolism and prevention of L-carnitine deficiency in patients with kidney disease undergoing haemodialysis. It has been shown to increase β-oxidation of fatty acids from the mitochondrial membrane. The perfusate will be supplemented with of L-carnitine 1 g/5 mL aqueous solution [37–40].Forskolin: This is a glucagon mimetic cAMP activator which results in increased lipolysis of lipid droplets and fatty acid oxidation [47]. The perfusate will be supplemented with 1 mg of NKH477 (water-soluble version of forskolin) in 2 mL of 0.9% sodium chloride (from a stock solution of 5 mg of NKH477 in 10 mL of 0.9% sodium chloride) [48, 49].Insulin: this will be infused at a 50% lower concentration than in the OrganOx instructions for use. This reduces the stimulation of de novo lipogenesis (DNL), the only source of fatty acid production in the liver during NMP [51].Glucose: the threshold to infuse parenteral nutrition (TPN) will be reduced from 10 mmol/L to 5 mmol/L. As glucose is a non-lipid precursor for DNL, this will reduce the liver’s ability to synthesise fatty acids de novo during perfusion [55].

Normothermic defatting will treat the liver in the ex-situ setting. Following treatment, prior to transplantation, the liver will be flushed with 2 L of preservation solution, as per standard NMP practice. The investigational agents will therefore be effectively removed from the liver prior to implantation.

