#### Mechanistic studies outcome measures

The identification of novel markers could augment current practice by predicting the outcome of each liver with objectivity. The mechanistic studies will test hypotheses based on previous published studies that have investigated markers in the field of NMP and will inform development of functional criteria and optimisation of future defatting protocols:To measure the effect of the intervention on the histological degree of steatosis:Histological quantification of MaS measured pre-perfusion, post-perfusion and during re-perfusion in the recipient. We hypothesise that the intervention of defatting will reduce the degree of MaS and severity of NAFLD activity score [75].To measure the effect of the intervention on markers on of hepatic lipid metabolism:Perfusate TG, insulin, ketone bodies and cytokines associated with IRI will be measured at baseline (pre-NMP) and during preservation (1, 2, 4 and 6 h and end of perfusion). Further measurements taken from the recipient peri-operatively (before transplant) and re-perfusion (following liver transplantation). This will provide insight into changes in intrahepatic lipid handling and inflammation. We hypothesise that the intervention of defatting will ‘repartition’ intrahepatic fatty acids away from esterification into oxidation pathways leading to a decrease in IHTG and a decrease in IRI-associated cytokine production [70].Perfusate FGF-21 will be measured at baseline (pre-NMP) and during preservation (1, 2, 4 and 6 h and end of perfusion). Further measurements taken from the recipient peri-operatively (before transplant) and re-perfusion (following liver transplantation). FGF-21 is a hormone produced in the liver involved in energy homeostasis; its secretion is attributed to metabolic stress. There is evidence that serum FGF-21 is a useful marker for steatosis and correlates with increasing steatosis grade [76]. We hypothesise that the defatting intervention will reduce FGF-21.To understand the structural, cellular and metabolic effects of defatting on steatotic livers.Genomic analysis of samples taken pre-perfusion, post-perfusion and following re-perfusion in the recipient:◦Transcriptomics: a complex signalling cascade regulates metabolic processes within the liver. To understand the effect of NMP and the defatting intervention, genomic analysis of liver tissue will be undertaken. We hypothesise that the defatting intervention will lead to downregulation in pathways related to fat synthesis and inflammation and an upregulation in pathways related to fat disposal. Samples from livers will undergo RNA sequencing of the liver and this will be correlated with clinical outcomes. Changes in gene expression will be mapped with changes occurring in biological pathways, inferring biological changes during NMP.Proteomic and glycomic analysis of perfusate samples taken at baseline (pre-NMP) and during preservation. Further measurements taken from the recipient peri-operatively (before transplant) and re-perfusion (following liver transplantation):◦Proteomics: a recent study investigating the use of NMP to increase utilisation of high-risk donor livers, identified protein clusters that were able to discriminate between transplantable and non-transplantable livers (22 out of 31) as well as markers predictive of post-transplant complications [77]. We aim to determine the effect of the intervention on protein expression associated with hepatic steatosis, inflammation and IRI.◦Glycomics: the liver perfusate glycome profile may form part of future functional criteria [78]. A recent study found that the abundance of a single glycan, agalacto core-alpha-1,6-fucosylated biantennary glycan (NGA2F) was significantly higher in the perfusate of livers that developed PNF. We will test this hypothesis in sequential perfusate samples.

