An ITT analysis will be performed for the primary outcome and secondary (donor liver related) outcomes. Secondary (recipient) outcomes will be analysed using a mITT approach. This analysis will exclude livers perfused but not transplanted for any reason.

For the mechanistic work, measures will be compared before and after perfusion to assess for a change during machine perfusion. A paired *t*-test will be used to compare the means of these levels pre- and post treatment to determine whether any change is statistically significant. For all analyses with statistical testing, a *p*-value of < 0.05 will be used to determine statistical significance.

Full details of the statistical analysis plan will be made available on the ISRCTN registry webpage (ISRCTN 14957538: 10.1186/ISRCTN14957538).

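### LiMAx after 6 h is read only in livers not yet accepted, and the mechanistic before/after test neither compares arms nor accounts for a 6 to 24 h perfusion time

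*Protocol article*

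**What the plan says.** **LiMAx.** After a first test following 1 h of stabilisation, it is "repeated at 5 h and subsequently every 6 h till end of perfusion where feasible". The protocol then adds: "If the decision to transplant has been made by 6 h of NMP, the test will not be repeated".

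**Perfusion time.** The defatting protocol runs "for a minimum of 6 h and a maximum of 24 h", and the control section gives the same limits. No section says what ends perfusion inside that window.

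**The decision to transplant.** Section {11d} states: "Transplantation of the liver will be based on ex-situ function and at the discretion of the implanting surgeon". Primary outcome measure adds that recipient factors also count and that the functional criteria do not bind the surgeon.

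**Mechanistic measures.** The stated aim is to measure the effect of the intervention on steatosis and on lipid metabolism. For steatosis the plan is "Histological quantification of MaS measured pre-perfusion, post-perfusion and during re-perfusion in the recipient". Section {33} confirms that liver biopsies are taken before perfusion, at its end and after reperfusion. Perfusate triglyceride, ketones, cytokines and FGF-21 are sampled pre-NMP, at 1, 2, 4 and 6 h, and at the end of perfusion. So is cfDNA, a clinical secondary outcome.

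**Analysis.** For the mechanistic work, section {20a} says "measures will be compared before and after perfusion to assess for a change during machine perfusion", by a paired t-test.

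**The concern.** Two separate weaknesses meet here.

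First, whether a LiMAx reading exists after 6 h depends on a decision taken after randomisation and partly on function. If defatting improves function, the livers still being tested late are an unequal selection from the two arms. An analysis cannot recover readings that were never taken.

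Second, the mechanistic section asks what the intervention does, but the analysis named for it asks only whether values change between the start and end of perfusion. Normothermic perfusion alone may change them. The background on animal studies reports a 30% fall in liver triglyceride in untreated rat livers, and macrovesicular steatosis falling from 28 to 15% in pig livers on perfusion alone. A change over time is therefore not evidence of a defatting effect, and the end sample has no common clock time.

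At stake are the secondary and mechanistic readings meant to inform functional criteria and future defatting protocols.

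**Working it through.** **1. When LiMAx is read.** Tests fall at about 1, 5, 11, 17 and 23 h. Every perfused liver is due to stay on the device for at least 6 h, so 1 h and 5 h are common to all. From 11 h on, only livers without a decision by 6 h contribute.

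**2. How many livers that might be.** The protocol gives no acceptance rate by 6 h. As an assumption, take the rates in Sample size {14} for meeting the 6 h criteria: 65% in controls, and 65 + 30 = 95% with defatting, 30 livers per arm. Expected number left = 30 × (1 − p).

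| Assumed accepted by 6 h (control / defatting) | Control left | Defatting left |
|---|---|---|
| 65% / 95% | 10.5 | 1.5 |
| 65% / 85% | 10.5 | 4.5 |
| 65% / 65% | 10.5 | 10.5 |

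At 95%, the chance that no defatted liver is left is 0.95^30 = 21%. The chance of at most one is 0.95^30 + 30 × 0.05 × 0.95^29 = 55%. The last row shows that no imbalance is expected if defatting has no effect on acceptance.

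**3. What selection does to the contrast.** Assume function at 6 h is normal with SD 1, that a liver is accepted when it exceeds a common threshold set at 0, and that late LiMAx has the same mean shift and correlates r with function at 6 h. The arm means are z(0.65) = 0.385 and z(0.95) = 1.645, a true difference of 1.26 SD. Among undecided livers each mean falls by r × φ(mean)/(1 − p). That is r × 1.058 in controls and r × 2.063 with defatting. The observed difference is then 1.26 − r × (2.063 − 1.058):

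- r = 0.3: 0.96 SD
- r = 0.5: 0.76 SD
- r = 0.8: 0.46 SD

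The contrast shrinks but keeps its sign. With one or two livers in one arm, imprecision is the larger problem.

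**4. Whether duration differs by arm.** Suppose accepted livers end at time tA and the others at tN, with the same 65% and 95%. Mean duration is p × tA + (1 − p) × tN, so the gap between arms is 0.30 × (tN − tA).

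| tA, tN (assumed) | Control mean | Defatting mean | Gap |
|---|---|---|---|
| 12 h, 12 h | 12.0 h | 12.0 h | 0 |
| 6 h, 12 h | 8.1 h | 6.3 h | 1.8 h |
| 8 h, 16 h | 10.8 h | 8.4 h | 2.4 h |
| 6 h, 24 h (both limits) | 12.3 h | 6.9 h | 5.4 h |

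Under this proxy the gap runs from none to 5.4 h. The documents do not say where in that range the trial would fall.

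**5. Which measures have a common time.**

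| Measure | Fixed time during perfusion? |
|---|---|
| LiMAx | Yes: 1 h, 5 h |
| Perfusate triglyceride, ketones, cytokines, FGF-21, cfDNA | Yes: 1, 2, 4, 6 h |
| Primary endpoint | Yes: 6 h |
| Liver histology, including macrovesicular steatosis | No: start, end, reperfusion only |

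**The case against.** The strongest reply has four parts.

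- The LiMAx rule stops a test, not the perfusion. Recipient factors affect the decision, and logistics could also set the duration, so a duration difference between arms is an inference. **This stands.**
- Most measures already have a common time at 5 h or 6 h, and the primary endpoint is fixed at 6 h. **This stands**, and it confines the timing problem to end-of-perfusion values, above all histology.
- The choice of main time point usually belongs in the analysis plan, and section {20a} promises very limited testing of secondary endpoints. **This stands in part.** The protocol itself fixes both the rule that stops LiMAx and the paired test. Neither is an omission left to a later document.
- The paired test makes no arm comparison, so it carries no between-arm bias. True, but that is also why it does not answer the question about the intervention.

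A reader might go further and infer that perfusion ends on acceptance, or that no end-of-perfusion measure can show a defatting effect. No section states the first, and the fixed-time samples rule out the second.

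A reader might also infer that the effect could reverse, because controls held longer might lose more fat. The human data cited in the background do not support this: 24 h of perfusion alone gave no histological reduction. The LiMAx calculation above shows attenuation, not a change of sign.

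Nor should a time course be extrapolated from the preclinical result that treatment "significantly reduced the amount of fat within the liver by 45% at 48 h". The same background reports structural and functional differences after 6 h, and Table 1 gives 40% at 6 h and 50% at 12 h for a different drug mixture. Steady linear loss fits neither.

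**Conclusion.** The point holds in limited form. LiMAx after 6 h comes from a subset selected after randomisation and cannot give an unbiased comparison of arms. The paired before/after test does not by itself measure the effect of the intervention that the mechanistic section asks about, and its end sample may fall anywhere from 6 to 24 h.

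In size, about 10.5 control and 1.5 defatted livers would have late LiMAx if acceptance by 6 h tracked the planned endpoint rates. That proxy is an assumption: the imbalance weakens with a smaller effect and vanishes with none. The shrinkage from 1.26 SD to between 0.96 and 0.46 SD rests on the normal model and the assumed correlations.

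This is a cheap improvement to secondary and mechanistic measures. The primary endpoint and the sample size are untouched.

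**What to change.** - Make LiMAx at 5 h, or its change from 1 h to 5 h, the between-arm comparison in all perfused livers. State that the 5 h test is done whatever has been decided, since the wording about a decision by 6 h can be read either way.
- For perfusate triglyceride, ketones, FGF-21, cytokines and cfDNA, compare arms on the 6 h value minus the pre-NMP value in all perfused livers. The paired test may stay as a description of change within arm.
- Label LiMAx after 6 h and end-of-perfusion perfusate values as descriptive.
- Report perfusion duration by arm and interpret the between-arm comparison of end-of-perfusion histology in its light. Do not rest a defatting claim on that histology if durations differ.

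The cost is wording in the outcome and analysis sections. The 5 h and 6 h readings are already scheduled, and Preservation parameters already records when perfusion starts and ends. The downside is that late readings lose inferential status.
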